### Secondary outcome measures

Improvement effects of TCLT in follow-up images will be measured by the Marshall computed tomography scale and Adams grading scale for DAI. The hemodynamic improvement effect of TCLT will be measured by transcranial Doppler (systolic and diastolic velocities of the left middle cerebral and basilar arteries, and pulsatility index and resistance index values).

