#### Gennarelli’s clinical classification

This is a classification of the severity of DAI with three levels: in mild DAI, coma lasts 6–24 h. In moderate DAI, coma lasts longer than 24 h but there is no abnormal posturing. In severe cases of DAI, the coma duration is longer than 24 h and signs of brain stem impairment (decortication or decerebration) can also be found [44].

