#### Secondary

Improvement in early and delayed functional outcomes measured by the GOSE after 1 and 6 months of the first stimulation.Improvement effects of TCLT in follow-up images measured by the Marshall computed tomography scale [60], the Adams grading scale [58], and Gennarelli’s clinical severity scale [44] for diffuse axonal injury.Hemodynamic improvement effect of TCLT measured by transcranial Doppler (systolic and diastolic velocities of the middle cerebral (MCA) and basilar arteries (BA) and the pulsatility index and resistance index values) [44]. It will be evaluated before stimulation and 1, 3, and 6 months after the first stimulation.

For GOSE 1 and 6 months after the first stimulation, a similar calculation of the primary variable outcome will be used.

Patients will repeat the CT scan and the MRI after 1 month of treatment, and they will be evaluated again for the following scales: Gennarelli’s, Adams’, and Marshall’s, and a comparison with image findings of the sham group will be performed.

The transcranial Doppler will analyze systolic and diastolic velocities of the MCAs and BAs and pulsatility index and resistance index values. The means and standard deviation will be calculated for these variables and compared with the first evaluation before stimulation.

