### Statistical analysis

The primary outcome variable will be analyzed with chi-square for comparison of dichotomized GOSE (favorable vs unfavorable) between intervention and sham. The second outcome measures for GOSE at 1 and 6 months after stimulation will be calculated in the same way as for the primary outcome measures. The results of the scales of DAI severity (Gennarelli’s), Adams, and Marshall will be compared with the results of the sham group with the Mann-Whitney *U* test. The second outcome measures related to hemodynamic evaluation will be analyzed with the *t* test for means and SD comparison of 1, 3, and 6 months with the basal value before stimulation.

The median and interquartile range will be calculated for age, intensive care unit days, hospitalization days, and days of treatment of infection. Gender, handedness, level of schooling, mechanism of injury, type of accident, sedation, pupils and presence of dysautonomia, presence of infection, and site of infection will be presented as absolute frequency, proportion, and confidence interval. The Glasgow Coma Scale score will be divided into four categories (3–5, 6–8, 9–12, 13–15) and will be expressed as absolute frequency, proportion, and confidence interval at four moments (scene, admission, discharged from ICU, and discharge from hospital).

Statistical Package for the Social Sciences software version 23.0 for Windows (Prentice Hall, Chicago, IL, USA) will be used for analyzing data. A significance level of *p* < 0.05 will be considered for data analysis.

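### Gennarelli's grade describes the acute coma, so it is not a valid 1-month improvement or imaging outcome to compare with sham

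*Protocol article*

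**What the plan says.** Three sections of the protocol article bear on this.

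- **Definition** (Instruments of evaluation, Gennarelli's clinical classification). The first two levels read: "in mild DAI, coma lasts 6–24 h. In moderate DAI, coma lasts longer than 24 h but there is no abnormal posturing". The third level is coma beyond 24 h with decortication or decerebration. Imaging plays no part, and no time is set for judging posturing.
- **Outcome** (Outcome variables, Secondary). One item begins "Improvement effects of TCLT in follow-up images measured by the Marshall computed tomography scale", goes on to the Adams scale, and ends with "Gennarelli’s clinical severity scale [44] for diffuse axonal injury". On timing: "Patients will repeat the CT scan and the MRI after 1 month of treatment", after which "they will be evaluated again for the following scales: Gennarelli’s, Adams’, and Marshall’s".
- **Test** (Statistical analysis). "The results of the scales of DAI severity (Gennarelli’s), Adams, and Marshall will be compared with the results of the sham group", using the Mann-Whitney U test.

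The shorter list under Secondary outcome measures, in the Background, gives only two scales for this purpose: "Improvement effects of TCLT in follow-up images will be measured by the Marshall computed tomography scale and Adams grading scale for DAI".

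**The concern.** The outcome is described as improvement on images, but the grade is a clinical record of the first hours and days after injury. Marshall and Adams grades can be read again from a new scan. Gennarelli's grade cannot, because its main criterion is the length of a coma that, for most patients, will have been classified long before the 1-month visit.

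At stake is the meaning of one secondary efficacy comparison. If the grade was settled before treatment could act, a small p-value would be a chance difference in injury severity between two arms of 16, reported as benefit. A large p-value would say nothing about the treatment.

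**Working it through.** The article gives no figure for this outcome (no expected distribution, effect or power), so there is none to reproduce. The check is mainly a comparison of the definition with the planned use.

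**1. What the grade needs as input.** It needs coma duration, with cuts at 6 h and 24 h, and the presence of abnormal posturing. The repeat CT and MRI provide neither.

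**2. What can change between the acute phase and 1 month.**
- Coma ended between 6 and 24 h: mild, and mild at every later scoring.
- Coma passed 24 h: moderate or severe. Elapsed duration cannot fall back below 24 h, so mild is out of reach however well the patient recovers.
- Moderate versus severe depends on posturing. If posturing at any time counts, the grade can only stay or rise. If posturing at the time of re-scoring counts, severe could become moderate. The article does not say which applies.
- No level describes a patient who has regained consciousness and function.

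On the coma criterion, then, the second scoring adds no information about recovery.

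**3. How much treatment can precede the 24 h cut.** Inputs:
- Sampling: coma of more than 6 h and admission less than 8 h after trauma. Patients who have awakened are not included.
- TCLT protocol: three sessions a week for 6 weeks, 3 × 6 = 18 sessions, all at the same time of day.
- Time of the first session: not stated.

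If sessions fall on different days at the same hour, two sessions are at least 24 h apart. A first session given after the 6 h coma requirement is met would put the second at 6 + 24 = 30 h or later. At most one session then precedes 24 h: 1/18 = 5.6%. The other 17/18 = 94.4% cannot affect whether a patient is mild. If the first session comes after 24 h, the share is 0/18.

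**4. What the test would pick up under each case.** These are simulations with 16 per arm and 6,000 runs. The grade mixes (mild/moderate/severe) are assumptions.
- Grade settled before treatment, same mix in both arms (20/40/40, 33/34/33 or 10/30/60): rejection in 4.7% to 4.9% of runs. This follows by construction, since both arms share one distribution. It restates the 5% level and is not independent evidence of a defect.
- First session before 24 h, and treatment assumed to move 10, 20, 30 or 40 percentage points of patients to mild from a sham mix of 20/40/40, taken equally from moderate and severe: rejection in about 8%, 18%, 34% or 56% of runs.

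The second case shows that a treatment signal is possible if a first session falls before 24 h and has an effect. That signal would be earlier awakening within the first day. It would not be improvement on images at 1 month or an effect of the six-week course.

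**The case against.** A reader might infer that the grade can never improve and that the comparison with sham tests nothing but baseline balance. The documents do not support either statement. Patients are enrolled while still in coma, from just over 6 h, and the time of the first session is not given. The 24 h cut may therefore be crossed after randomization, and possibly after a first session. With no time set for posturing, a current-status reading could also move severe to moderate. These points stand, and the conclusion is limited to match.

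A reader might also take the shorter list under Secondary outcome measures as proof that the scale was never meant as an outcome. That list is a summary. It also leaves out the GOSE at 1 and 6 months and names only the left middle cerebral artery, so the omission shows little.

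Nor does the article say that awake patients would be left ungraded or dropped at 1 month. It gives no level for them, but how they would be handled is unknown.

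Finally, an article condenses the full protocol, and a detailed scoring rule could be there. The outcome, the time of re-scoring and the test are nevertheless fixed in this text and do not fit the definition it gives. No scoring rule would let a scan supply coma duration or let elapsed duration shorten.

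**Conclusion.** The point holds in this form: Gennarelli's grade, as the article defines it, is not a valid 1-month improvement or imaging outcome. On the coma criterion the second scoring cannot show recovery. The comparison with sham reflects acute injury severity wholly if the first session comes after 24 h, and largely if it comes before, when probably at most 1 of 18 sessions (5.6%) could bear on the mild grade.

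This rests on two assumptions: that sessions fall on different days at the same hour, and that posturing is read as a sign of the acute coma. If posturing is instead judged at 1 month, the moderate–severe distinction could move, but it would still be one clinical sign and not an image finding.

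The effect is confined to one secondary comparison. The primary outcome, the sample size and the other secondary outcomes are untouched. It should be corrected, because the plan as written would produce an efficacy statement that the measure cannot support.

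**What to change.** - In Outcome variables, Secondary: remove Gennarelli's scale from the efficacy item and from the scales scored again after 1 month. Keep Marshall and Adams as the imaging scales.
- In Statistical analysis: remove Gennarelli's scale from the Mann-Whitney list.
- Report the grade once, by arm, as a descriptor of acute injury severity. State when coma duration and posturing are recorded. Because the 24 h cut may fall after randomization, label it acute severity and not pre-randomization baseline.

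A separate coma-recovery outcome would be an optional addition and is not needed to correct this point.

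The cost is wording in two sections and one fewer listed secondary outcome. No new data are needed.

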### Baseline measures

Complementary data will be assessed from all the patients:Sociodemographic characteristics: age (years), gender (male/female), handedness (right/left/ambidextrous), level of schooling (none, preschool, elementary school, middle school, high school, tertiary or higher school), occupation statusCharacteristics related to the trauma: mechanism of injury, type of accidentCharacteristics at admission: sedation (no/yes), pupillary abnormalities (both pupils reactive, one reactive, and none reactive to light), Glasgow Coma ScaleCharacteristics during hospital stay: ICU days, hospitalization days, infection during hospitalization (no/yes, site of infection, days of treatment), Glasgow Coma Scale at the trauma scene, at admission, at discharge from the ICU (or death), at discharge from hospital (or death)Presence of dysautonomia related to DAI

The mechanisms of injury which will be considered are as follows: blow to the head (direct impact), acceleration-deceleration forces (wherein no direct impact is required), and concussive forces (blast waves from explosions).

The types of accident are as follows: motor vehicle collisions, motorcycle crashes, pedestrians struck by automobiles, falls, explosions.

Dysautonomia is a syndrome characterized by episodes of autonomic dysregulation, leading to an increased heart rate, respiratory rate, and body temperature and other symptoms. It can be defined by simultaneous occurrence of five of the following features [49]:Increased heart rate (>120/min)Increased respiratory rate (>24/min)Raised temperature (>38.5 °C)Increased systolic blood pressure (>160 mmHg)Increased muscle tone (Modified Ashworth Scale score)Decerebrate or decorticate posturingProfuse sweating

### Electronic data collection

Data collected will be stored in a database developed with the Research Electronic Data Capture system [64]. It is hosted on the server of the University of São Paulo. It is a software developed at Vanderbilt University (TN, USA). This is a fully Web-based software that enables electronic data collection and also study process management. It also respects the international policies on data privacy and security in the health sector [65].

### Blinding and allocation concealment committee

In the present study, there is a medical committee who can remove blinding, if something unexpected happens: a major adverse event, patient dropout, etc. The medical committee is not directly related to any patient group.

### Sample size calculation

The previously published studies about transcranial LED therapy are case reports or case series. Besides, there is no study which evaluated transcranial LED therapy for acute severe TBI patients. Considering these facts, the sample size was calculated based on the primary outcome proportion difference (favorable vs unfavorable) on chi-square with the estimation of effect size (Cohen’s *D*) of 0.5, alpha of 5%, and statistic power of 80%. The final result was 32 patients, who will be divided into two groups (16 patients each).

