### Randomization and blinding

The randomization process will be achieved through a computer software, respecting a 1:1 ratio for the 30 patients. The method of randomization used by the computer software is random permuted block sizes of 2. The two groups will be active coil and sham coil. As this is a double-blinded study, neuropsychologists and patients (as well as their relatives) will be blinded to the group assignment. The method of blinding will consist of using an equal helmet for both the intervention and placebo groups. Both helmets will emit a red light, but only the active coil group will receive LED emission (intervention group).

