**Fig. 2 Fig2:**
[figure not shown]
Study protocol flow diagram. Thirty patients who meet the inclusion and exclusion criteria will be recruited from the Emergency Department of University of São Paulo General Hospital. After baseline data collection, GOSE evaluation, transcranial Doppler hemodynamic measures, and CT scan, these patients will be randomized at a 1:1 ratio: active coil group vs sham coil group. They will be submitted to 18 sessions of TCLT three times per week and reevaluated with the aforementioned instruments after 1, 3, and 6 months after trauma

During the TCLT sessions, patients will remain seated in bed with head support and with their eyes protected. Eighteen sessions will be carried out, with a total of 56 applications. The same qualified previously trained therapist will perform all TCLT sessions at the same time of the day.

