Moderate TBI patients were treated with a high-power NIR laser (10–15 W at 810 and 980 nm) through 20 NIR applications over a 2-month period. They showed decreased headache, depression, anxiety, and insomnia, whereas cognition and quality of life improved, accompanied by changes in the SPECT imaging [70].

After 18 TCLT treatments (26 J/cm^2^ per LED cluster head placement red/NIR, 500 mW, 22.2 mW/cm^2^) in left-hemisphere stroke patients with chronic aphasia, resting-state fMRI scans have been obtained and shown significant increases in “naming ability” [10].

The 3-month period was chosen for the primary outcome because it presents an important relationship with the first year’s outcome. The usual result expected for severe TBI patients is about 30% of favorable outcome at 3 months [71]. Considering a strong size effect for the intervention, we expect a treatment effect of 50 percentage points (difference in the favorable-outcome rate of 30% vs 75%).

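### The effect size, the expected rates and the number of patients do not agree: 32 patients give 80% power for 30% vs 80%, but only about 72–76% for the 30% vs 75% also stated, and two places give N as 30

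*Protocol article*

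**What the plan says.** All references are to the protocol article.

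- **Sample size calculation.** The basis is described as "the sample size was calculated based on the primary outcome proportion difference (favorable vs unfavorable) on chi-square with the estimation of effect size". The effect size is 0.5, labelled Cohen's D, and the remaining inputs and the result are given as "alpha of 5%, and statistic power of 80%. The final result was 32 patients", 16 per arm. No event rates are given in this section.
- **Statistical analysis.** "The primary outcome variable will be analyzed with chi-square for comparison of dichotomized GOSE (favorable vs unfavorable) between intervention and sham".
- **Discussion.** The usual favorable-outcome rate at 3 months in severe TBI is put at about 30%. The text continues: "we expect a treatment effect of 50 percentage points (difference in the favorable-outcome rate of 30% vs 75" percent). This is the only place where the expected effect is expressed as rates.
- **Number of patients.** The Abstract, Recruitment and Sample size calculation give 32. Randomization and blinding has "respecting a 1:1 ratio for the 30 patients", and the Fig. 2 legend has "Thirty patients who meet the inclusion and exclusion criteria will be recruited".

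**The concern.** Three things that should describe one design do not match. The effect-size label does not fit the test or the total. The Discussion gives a difference and a pair of rates that cannot both be true, since 75 − 30 = 45. The total is 32 in three places and 30 in two, one of which describes how the allocation is generated.

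This is the only power justification for the primary outcome. If 30% vs 75% is the effect the trial was meant to detect, a null result would be read as coming from a trial with 80% power when the true figure is lower. If the allocation list is built for 30, power falls a little further under either effect.

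**Working it through.** **Inputs.** Two-sided alpha 0.05 (sidedness is not stated, but a 1-df chi-square test is two-sided), power 80%, effect size 0.5 and N = 32 come from Sample size calculation. The rates 30% and 75% and the 50-point difference come from the Discussion. N = 30 comes from Randomization and blinding and from Fig. 2.

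**1. Reproducing the 32.** For a 1-df chi-square test the non-centrality parameter is N·w², and 80% power at 5% needs (1.960 + 0.842)² = 7.849.
- 0.5 read as w: N = 7.849 / 0.25 = 31.4, rounded up to 32. Power at N = 32 is 80.7%.
- 0.5 read as d (two means): 63 per arm.
- 0.5 read as h (arcsine difference): 2 × 7.849 / 0.25 = 62.8, so 63 per arm.

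The figure of 32 is therefore sound for w = 0.5, and the label is wrong.

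**2. What w = 0.5 means as rates.** With equal arms, w = (p₂ − p₁) / (2√[p̄(1 − p̄)]), where p̄ is the mean of the two rates. Setting p₁ = 0.30 and w = 0.5 gives p₂ = 0.798, or about 80%.
- 30% vs 80%: w = 0.50 / (2√[0.55 × 0.45]) = 0.503. N = 7.849 / 0.2525 = 31.1, rounded up to 32.
- 30% vs 75%: w = 0.45 / (2√[0.525 × 0.475]) = 0.451. N = 7.849 / 0.2030 = 38.7, so 39, or 40 with equal arms. The pooled two-proportion formula gives 19 per arm (38).

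**3. Power at the planned sizes.** The non-central column uses N·w². The exact column enumerates both binomial distributions for the uncorrected Pearson test.

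| Rates | N | N·w² | Non-central chi-square | Exact Pearson |
|---|---|---|---|---|
| 30% vs 75% | 32 | 6.50 | 72.2% | 75.8% |
| 30% vs 75% | 30 | 6.09 | 69.4% | 71.1% |
| 30% vs 80% | 32 | 8.08 | 81.1% | 85.3% |
| 30% vs 80% | 30 | 7.58 | 78.6% | 81.5% |

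At N = 32 the shortfall for 30% vs 75% is 80 − 75.8 = 4.2 points (exact) to 80 − 72.2 = 7.8 points (non-central). Using 30 patients costs a further 3 to 5 points for 30% vs 75%, and 3 to 4 points for 30% vs 80%.

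**The case against.** The strongest reply is that the sample size section contains no arithmetic error. It gives no rates, its 32 follows from w = 0.5, and the 50-point figure in the Discussion agrees with it once the 30% base rate is applied. On that reading the 75% is a slip and the stated power is delivered. This stands. A reader might infer that the trial is simply underpowered for the effect it expects, but the article states two effects and only one of them falls short. For the same reason it would be wrong to insist that the difference be corrected to 45 points: changing 75% to 80% removes the contradiction equally well.

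A second reply is that 32 can be reached from 30% vs 75% by another route. The unpooled two-sided normal formula gives 7.849 × (0.30 × 0.70 + 0.75 × 0.25) / 0.45² = 15.4, so 16 per arm. But that is not the calculation described, which starts from an effect size of 0.5 and a chi-square test, and exact power of the uncorrected test at 16 per arm is still only 75.8%.

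Three stronger readings are tempting, and the article does not support them.
- **Power of about 62%.** This is the figure at 16 per arm for 30% vs 75% under Yates' correction or Fisher's test. The article names neither. It says chi-square, and the version of the test is a detail commonly left to the analysis plan.
- **A sham rate above 30%.** Eligibility excludes some poor-prognosis patients, so a higher rate is possible. But the Background calls DAI the most common cause of persistent vegetative state and severe disability in TBI, so the direction is uncertain. Any alternative rate would be an assumption.
- **An ordinal analysis of the GOSE is needed.** The article pre-specifies the dichotomy and gives reasons for it. Preferring another analysis is a design opinion and does not show an error.

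**Conclusion.** The point holds as an inconsistency among figures that the trial relies on. The effect size is mislabelled: 32 follows from 0.5 only as Cohen's w. The Discussion contradicts itself by 5 percentage points, and that decides whether the stated 80% is met. Power with 32 patients is about 72–76% if 30% vs 75% was meant, and 81–85% if 30% vs 80% was meant. The article does not show which was intended. N is 32 in three places and 30 in two.

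The size is moderate: a shortfall of 4 to 8 points under the less favorable reading and none under the other, with N = 30 taking off roughly 3 to 5 more. These figures assume a two-sided 5% uncorrected chi-square test, equal arms, a 30% control rate and complete 3-month outcomes.

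**What to change.** 1. In Sample size calculation, replace Cohen's D with Cohen's w and add the two rates that the value represents.
2. In the Discussion, choose one effect and use it throughout. Either state 30% vs 80% (50 points) as the design effect and keep the 80% power statement, or keep 30% vs 75% (45 points) and restate power as about 72–76% with 32 patients. The sponsor must say which was intended.
3. Use 32, as in the sample size section, in Randomization and blinding, the Fig. 2 legend and the allocation list itself.

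The cost is wording. No extra patients are needed, and the test, endpoint and design are unchanged. The only possible loss is a less favorable power figure, if 30% vs 75% is kept.
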